## Abstract

**Background:**

The objective of this study is to evaluate the antihypertensive effect of bedtime administration of low doses of aspirin in patients with treated hypertension and high cardiovascular risk on low-dose aspirin for secondary prevention, in order to optimize their usual treatment and reduce their cardiovascular risk.

**Methods/Design:**

This is a prospective phase IV multicentre, randomised, triple-blind, placebo-controlled, cross-over clinical trial. We will include 258 individuals with hypertension treated with low-dose aspirin for secondary prevention. These patients will be randomly recruited, by approximately 40 primary care physicians collaborating in the study, mainly in the Guipúzcoa West, Bilbao and Barcelona areas. The 258 patients will be randomly allocated to treatments to create two comparable groups. In the first period, the intervention group will take aspirin at night and placebo in the morning, while the control group will take their aspirin in the morning and placebo in the evening for 2 months. After a washout period of 15 to 30 days, there will be a second 2-month period for which groups will swap treatments. Participants will undergo ambulatory blood pressure monitoring at baseline, at the end of first period and then again at the beginning and end of the second period. The main outcome measure is the change in mean blood pressure over 24 h, and as secondary outcomes we will also assess changes in systolic and diastolic blood pressure, during the day and night, and the relationship between them. Lastly, we will explore whether non-dipper patients convert into dippers with the intervention.

**Discussion:**

The goal of this research is to provide the scientific basis for indicating a change in the time of aspirin administration from morning to evening, by primary health practitioners, to improve the patient control of blood pressure and more effectively reduce their cardiovascular risk, by combining this hypotensive effect with the well-known anti-platelet effect of low-dose aspirin.

**Trial registration:**

ClinicalTrials.gov NCT01741922

## Background

In the last decade, several interesting studies have been published demonstrating the hypotensive effect (7/4 mmHg) of low-dose acetylsalicylic acid (ASA) administered in the evening. These effects are not observed if the ASA is administered at other times of day [1-3]. Further, it has been reported that 58% of non-dipper patients become dippers under evening administration of ASA [2]. These authors attribute the phenomenon to the inhibitory effect of ASA on angiotensin II, by the release of nitric oxide (NO) from the vascular endothelium, being 30% stronger when ASA is administered in the evening [2,3].

To the best of our knowledge, trials reported in the literature have all been carried out in healthy or mildly hypertensive individuals who were not under treatment for hypertension prior to the study [1,3,4]. On the other hand, millions of hypertensive patients across the world take ASA for secondary prevention, usually in combination with other drugs. Despite this, researchers have not included these patients in trials to assess the hypothetical hypotensive effect of bedtime ASA. It therefore remains to be determined whether the observed effect is reproduced in patients with a medical history of cardiovascular events, the very individuals who are often prescribed low-dose ASA [5-8].

The great importance of controlling blood pressure (BP), as a cardiovascular risk (CVR) factor is very widely recognised [9,10]. In addition, it has been demonstrated that morbidity and mortality are lower among individuals whose BP falls more at night [11-13], one study finding that a decrease of 5% in the magnitude of the night-time dip increased mortality by 31% [14]. Despite the broad range of antihypertensive agents available, efforts of healthcare professionals and extensive research on the subject, the control of BP still represents a challenge and is not always achieved. In the 2010 PRESCAP study, only 46% of patients had good control of their systolic and diastolic BP, despite the fact that 63% were on more than one antihypertensive drug [15]. It is, therefore, clear that any drug treatment that could contribute to the control of BP should be investigated and, particularly, when the drug involved, ASA, is already widely used.

If the hypotensive effect of taking low-dose ASA at bedtime were to be confirmed, this would be an important advance for these patients as, without adding new drugs to their regimen (with potential adverse effects) and with minimal inconvenience, we would be able to improve the control of their BP and more effectively reduce their cardiovascular risk by combining this hypotensive effect with the well-known antiplatelet effect of low-dose ASA.

## Methods/Design

### Objectives and hypothesis

#### Objectives

The general objective of the study is to assess the hypotensive effect of administering ASA at bedtime instead of during the day, in hypertensive patients under preventative treatment with low-dose ASA and a history of cardiovascular events. This general objective can be broken down into several specific objectives:

•To quantify the change in blood pressure associated with the bedtime administration of low doses of ASA in hypertensive patients with history of cardiovascular events and who have been regularly taking this drug during the day for secondary prevention

•To measure the night-time dip in BP after bedtime administration of ASA at low doses

•To explore any changes in the circadian pattern of BP, after changing the time when ASA is taken, and the potential transformation of non-dippers to dippers

•To investigate potential differences in the hypotensive effect of bedtime administration of low-dose ASA in various different subgroups by age, sex, serum creatinine levels, et cetera

•To investigate potential differences in the hypotensive effect of bedtime administration of low-dose ASA as a function of the antihypertensive treatment given to patients

•To investigate potential changes in adverse effects when ASA is taken at bedtime rather than during the day

#### Hypotheses

In hypertensive patients on low-dose ASA for secondary prevention, mean BP will fall by at least 5 mmHg if the drug is taken at bedtime rather than at another time of day. Further, these individuals will improve control of their BP, which is one of their main CVR factors.

The percentage fall in mean night-time BP will be higher among non-dippers than among individuals already classed as dippers. The percentage of individuals who are dippers will increase among the patients undergoing the intervention (with the change in the time of day low-dose aspirin is taken).

At least 40% of non-dippers in the study will become dippers on changing the time of they take their aspirin (Figure 1).

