### Evaluation of results

The primary outcome measure will be the mean blood pressure (MBP), and the secondary outcome measures will be the systolic and diastolic BP, HR and pulse pressure (PP). All of these will be measured over 24-h periods with a clinically-validated ABPM device, Watch BP 03. The research nurses will fit this ABPM device on patients and remove it after the 24-h measurement period, having first measured the patient’s BP with a validated OMRON M6 blood pressure monitor twice, or three times if the difference between the first two measurements is >5 mmHg. After that, they will give patients a notebook to record their activity, exercise and meals times as well as the time they go to bed and wake up during the 24 h of monitoring.

The systolic and diastolic BP as well as the HR will be measured every 20 min between 07:00 and 23:00 and every 30 min between 23:00 and 07:00. Monitoring will not be considered valid if >30% of the data are missing or if there is no data for a period >2 h. It will also not be considered valid if the patient has an irregular sleep-wake rhythm, with resting times >12 h or <6 h per night, during the monitoring period [17]. We will define the daytime BP as the mean of the measurements collected between 09:00 and 21:00 and the night-time BP as the mean of the measurements taken between 0:00 and 06:00, as this is the timetable that most closely matches the habits of most of our patients.

In addition, we will calculate the night/day ratio of the BP and classify patients according to this value ratio : >1, riser; >0.9 and ≤ l, non-dipper; >0.8 and ≤ 0.9 dipper; and ≤ 0.8, extreme dipper.

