### Sample size

A sample size of 258 patients, with 129 in each group, will provide a statistical power >80% for detecting as significant (*P*< 0.05) a difference of 2.5 mmHg between the mean arterial pressure with bedtime and daytime administration, using a two-tailed Student’s t-test (standard deviation obtained from previous studies, with similar populations to that of our project and estimated to be 8 mmHg) [4].

A reduction of 5 mmHg in arterial pressure is considered to be clinically significant at the individual level, since it is associated with a decrease of 12.5% in the risk of cardiovascular events and of 16.7% in the risk of acute cerebrovascular accidents [7]. We expect that with bedtime administration at least 50% of patients will achieve this level of reduction in BP, and that there will be no changes during day-time administration. Under this assumption, the mean difference between the two groups would be at least 2.5 mm/Hg.

These calculations are based on the formula for calculating sample sizes in cross-over clinical trials developed by Donner (1984) [18]. It has been assumed that around 5% of the BP measurements will not be valid, that around 15% will be lost to follow-up and that the intra-subject correlation will be 0.5.

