### Analysis

First, an assessment will be made of the potential carry over effect of the treatment from the first period to baseline levels before the second period. The analysis will be carried out on an intention-to-treat basis, comparing the mean blood pressure at the end of the period of bedtime intake with that observed after the daytime intake, adjusting for the baseline blood pressure at the start of each period in all patients which at least have received one dose of treatment. Moreover, we will perform a per protocol analysis with only the patients have not change in their treatment within the 5-month period of the trial and have not been withdrawn. The effect attributable to bedtime intake will be estimated in terms of the difference in mean blood pressure between the two periods and the 95% confidence interval will be calculated using mixed-effect models analysis of covariance for repeated measures of blood pressure taken in each subject at the end of each of the periods. These models will include the patient as a random effect (intercept), to take into account the correlation between the two measurements in the same individual in each period. As well as adjusting for the baseline levels, we will adjust for potential confounding or modifying variables: changes in medication, period or sequence, age, sex, unhealthy habits as to be smoker or no smoker, risk factors as to be dipper or non-dipper comorbidity as diagnosis of dyslipemia, diabetes, stroke, peripheric arteriophaty or myocardial infarction and month of the year when the study is started. We will assess, by means of tests of interaction, the absence of a modifying effect of bedtime intake as a function of the period when patients took the ASA at this time.

A stratified analysis will be undertaken considering two groups, dippers and non-dippers, assuming that the prevalence of non-dippers in this population is 40%.

In the mixed-effect analysis, all the data available from each of the subjects included in the study will be considered, regardless of whether there is missing data. Values of missing data will not be imputed, except in the case of the baseline values for the second period, in which case they will be assigned the same value as the baseline measurements at the start of the study. It has been shown that this is more robust than other approaches to dealing with missing data.

All this analysis will be carried out using the SAS statistical package.

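### The target that at least 40% of non-dippers become dippers has no daytime comparator, so reaching it would not show a bedtime effect

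*Protocol article*

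**What the plan says.** The Hypotheses section of the protocol article makes three statements about dipping status:

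- A conversion target: "At least 40% of non-dippers in the study will become dippers on changing the time of they take their aspirin".
- A comparison of strata: "The percentage fall in mean night-time BP will be higher among non-dippers than among individuals already classed as dippers".
- A rise in the overall share of dippers: "The percentage of individuals who are dippers will increase among the patients undergoing the intervention".

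None of the three names the daytime period as comparator. Elsewhere conversion is presented as exploratory: the abstract says "we will explore whether non-dipper patients convert into dippers with the intervention", and the Objectives use similar language.

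The section Evaluation of results classifies patients by the night/day ratio of blood pressure. Above 1 is a riser, above 0.9 up to 1 a non-dipper, above 0.8 up to 0.9 a dipper, and 0.8 or less an extreme dipper.

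The Analysis section compares blood pressure at the end of bedtime intake with that at the end of daytime intake, adjusted for each period's baseline. It then adds: "A stratified analysis will be undertaken considering two groups, dippers and non-dippers", with an assumed non-dipper prevalence of 40%. It describes no analysis of conversion. The one interaction test it describes asks whether the bedtime effect depends on the period in which it was given.

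**The concern.** A group selected for lying above a cut-off on a variable measurement will partly fall below that cut-off when measured again, whether or not treatment works. An absolute conversion rate adds this regression to the mean to any true effect. If the no-effect rate is close to 40%, the hypothesis could be declared confirmed when dosing time has no influence. If it is lower, the observed rate still overstates what bedtime dosing achieved. The Discussion gives conversion clinical weight, so a figure reported against this target would probably be read as evidence of a benefit.

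The comparison of strata raises a smaller, separate point. Saying that non-dippers respond more than dippers is a statement about a difference between two effects. Two stratum estimates side by side do not test that difference.

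**Working it through.** **The plan's own figure.** The protocol gives no derivation for the 40% target, so there is nothing to reproduce. The sample-size calculation concerns mean arterial pressure and does not bear on conversion.

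**Inputs**

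- Prevalence of non-dippers p = 0.40 (Analysis: "assuming that the prevalence of non-dippers in this population is 40" per cent).
- Correlation between two monitorings of the same patient r = 0.5 (Sample size: "the intra-subject correlation will be 0.5"). This is stated for mean arterial pressure. The document gives no correlation for the night/day ratio, so its use here is an assumption and r is varied below.
- Treatment effect: none, by construction.
- Patients: 258 (Sample size).

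**Model.** The ratio is taken as bivariate normal at two monitorings, with the same margins and correlation r. Everything above the cut-off counts as non-dipper and everything at or below it as dipper.

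- Cut-off in SD units: the 60th percentile, t = 0.2533.
- No-effect conversion = 1 − P(X1 > t, X2 > t) / p.
- At r = 0.5, P(both above) = 0.2391, so conversion = 1 − 0.2391/0.40 = 0.402.

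**Range over the unknown correlation, p = 0.40**

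| r | P(both above) | no-effect conversion |
|---|---|---|
| 0.3 | 0.2058 | 48.5% |
| 0.4 | 0.2221 | 44.5% |
| 0.5 | 0.2391 | 40.2% |
| 0.6 | 0.2574 | 35.6% |
| 0.7 | 0.2776 | 30.6% |
| 0.8 | 0.3009 | 24.8% |

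**Chance of reaching 40% with no effect (binomial).** The expected number of non-dippers is 258 × 0.40 = 103. Allowing for 5% invalid measurements and 15% loss to follow-up, it is 258 × 0.80 × 0.40 = 82.6, or 258 × 0.95 × 0.85 × 0.40 = 83.3. For 82 to 103 non-dippers the chance is:

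- r = 0.4: 0.78 to 0.81
- r = 0.5: 0.49 to 0.54
- r = 0.6: 0.16 to 0.22
- r = 0.7: 0.02 to 0.04

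**Sensitivity to the four classes, at r = 0.5.** The document gives no shares for risers or extreme dippers, so these are assumed. Counting 5% to 15% risers apart from non-dippers gives about 36% to 48%. Not counting an assumed 10% of extreme dippers as dippers gives 37.7%.

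**Overall percentage of dippers.** At r = 0.5, the share of dippers who become non-dippers is 0.40 × 0.402 / 0.60 = 26.8%. The flows balance: 0.40 × 0.402 = 0.161 and 0.60 × 0.268 = 0.161. Prevalence stays at 40%, so reclassification alone does not produce a rise in the share of dippers.

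**Night-time fall by stratum.** Within baseline non-dippers, regression to the mean affects the end-of-bedtime and the end-of-daytime measurement alike, and it largely cancels in their difference. The same holds within dippers. The planned bedtime-versus-daytime contrast is therefore protected; only a change from baseline would not be.

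**The case against.** The strongest reply is that the 40% is an expectation and not a decision rule. It appears once, under Hypotheses. The Analysis section contains no test against it, the abstract and Objectives call conversion exploratory, and the full analysis of conversion may sit in a document not shown. This stands as far as it goes: the missing conversion analysis is not counted here as a fault, and the weight of the point is limited. It does not rescue the sentence itself, which fixes a number that cannot be interpreted without a comparator.

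A second reply is that the trial is a randomised, blinded crossover, so nothing in it is uncontrolled. That is right about the trial. Each patient has an end-of-daytime monitoring, and the primary comparison uses it. The defect lies in how one hypothesis is worded.

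A third reply is that the match between 40.2% and 40% rests on a borrowed correlation and on collapsing four classes into two. That also stands, so the figure is illustrative and the range matters. At a correlation of 0.7 or more, chance alone would rarely reach 40%. But the document gives no value for the ratio, and even at 0.8 about a quarter of non-dippers would change class with no effect. Nor does it say which baseline monitoring defines dipper status; that classification rests on a single 24-hour recording is an inference.

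A reader might go further and infer that every dipper hypothesis is biased in the same way, including the larger night-time fall in non-dippers. The document does not support that. The stratified analysis follows a bedtime-versus-daytime comparison in which regression to the mean largely cancels, and the overall dipper percentage is not moved by reclassification. What remains for the strata is only that the difference between them needs a test. The Analysis section lists dipper status among confounding or modifying variables, but the only interaction test it describes concerns period.

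**Conclusion.** The point holds for the conversion hypothesis. As worded, reaching 40% would not demonstrate an effect of bedtime dosing. With the plan's 40% prevalence and a bivariate normal ratio, no-effect conversion is about 40% if the correlation of 0.5 carries over from mean arterial pressure, and runs from about 49% to 25% for correlations of 0.3 to 0.8. It would be wrong to say that the plan's own figures establish 40%, because the correlation of the ratio is not given.

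A smaller point holds beside it: the claim that non-dippers respond more than dippers needs a direct test of the difference.

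Both concern exploratory or secondary hypotheses. Neither the primary analysis nor the hypothesis on the overall percentage of dippers is shown to be biased by regression to the mean.

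**What to change.** Replace the absolute 40% with a within-patient comparison. Among patients who are non-dippers at baseline, compare the proportion classed as dippers at the end of the bedtime period with the proportion at the end of the daytime period, using a mixed logistic model with a term for period or a paired test. State which baseline monitoring defines the group, and whether risers count with non-dippers and extreme dippers with dippers.

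Test the claim of a greater night-time fall in non-dippers as a treatment-by-baseline-dipper-status interaction on end-of-period night-time blood pressure, not on change from baseline. Report the stratum estimates alongside it.

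The cost is a change of wording in the hypotheses and the analysis. Both analyses use monitorings that the design already schedules, and no patient, visit or measurement is added.

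### The 40% non-dipper conversion hypothesis has no daytime comparator, so reaching 40% would not in itself show an effect of bedtime aspirin

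*Protocol article*

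**What the plan says.** - **Hypotheses:** "At least 40% of non-dippers in the study will become dippers on changing the time of they take their aspirin". No comparator is named. By contrast, the mean blood pressure hypothesis in the same section is worded as bedtime against another time of day.
- **Objectives:** conversion to the dipper class is a specific objective, in exploratory terms: "To explore any changes in the circadian pattern of BP, after changing the time when ASA is taken, and the potential transformation of non-dippers to" […]. The abstract likewise says "we will explore whether non-dipper patients convert into dippers with the intervention".
- **Evaluation of results:** each patient is classed by cuts on the night/day ratio: above 1 riser, above 0.9 and up to 1 non-dipper, then ">0.8 and ≤ 0.9 dipper; and ≤ 0.8, extreme dipper".
- **Analysis:** the bedtime-versus-daytime comparison is described for mean blood pressure. Dipper status appears as an adjustment variable and as a stratum, "assuming that the prevalence of non-dippers in this population is 40"%, but not as an outcome compared between treatments.
- **Sample size:** the calculation for mean arterial pressure assumes that "the intra-subject correlation will be 0.5". No correlation is given for the night/day ratio.

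**The concern.** A group picked out because one noisy reading lies above a cut will partly lie below it on the next reading, with or without treatment. A conversion percentage measured against baseline therefore mixes this regression to the mean with any real effect. If the chance component is itself near 40%, a null treatment could appear to meet the stated hypothesis.

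The matter is not peripheral. The Discussion gives conversion great weight and links an improved circadian pattern to lower cardiovascular risk. A conversion figure read against 40% could support a claim about circadian pattern that the trial had not shown. The cross-over already supplies the control, because each patient is recorded at the end of both timings.

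**Working it through.** The article gives no derivation for its 40% threshold, so there is no figure to reproduce. The check asks how often non-dippers would convert with no treatment effect.

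**Inputs from the article**
- Prevalence of non-dippers: 40% (Analysis).
- Cut: ratio >0.9 (Evaluation of results).
- Sample size 258, with about 5% invalid measurements and about 15% lost (Sample size).

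**Assumptions made here**
- The ratio at two recordings is bivariate normal with the same mean and variance (no effect).
- Status is assigned at the first baseline recording; the article does not say which recording is used.
- The 40% prevalence covers every ratio above 0.9, risers included.
- The ratio's correlation ρ between recordings is unknown, so 0.3 to 0.8 is shown.

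**Step 1: evaluable non-dippers.** 258 × 0.80 × 0.40 = 82.6, or 258 × 0.95 × 0.85 × 0.40 = 83.3. Take 82 and 83.

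**Step 2: null conversion.** The standardised cut is c = Φ⁻¹(0.60) = 0.2533, and

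conversion = 1 − P(X₁ > c, X₂ > c) / 0.40.

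At ρ = 0.5 the joint probability is 0.2391, so conversion = 1 − 0.2391/0.40 = 40.2%.

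**Step 3: chance of observing at least 40%.** Exact binomial tail: at least 33 of 82, or at least 34 of 83.

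| Assumed ρ | Joint probability | Null conversion | P(≥40%), n = 82 | P(≥40%), n = 83 |
|---|---|---|---|---|
| 0.3 | 0.2058 | 48.5% | 95% | 93% |
| 0.4 | 0.2221 | 44.5% | 81% | 77% |
| 0.5 | 0.2391 | 40.2% | 54% | 49% |
| 0.6 | 0.2574 | 35.6% | 22% | 18% |
| 0.7 | 0.2776 | 30.6% | 4% | 3% |
| 0.8 | 0.3009 | 24.8% | 0.1% | 0.1% |

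The two last columns differ mainly because 40% of 82 and of 83 round up to different counts. Null conversion reaches 40% only for ρ of about 0.505 or lower.

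**Step 4: sensitivity to class definition.** If risers are left out of the starting group, then at ρ = 0.5 with an assumed ratio SD of 0.06 to 0.10, 42–46% move to 0.9 or below, and 35–40% move into the dipper band alone (above 0.8, up to 0.9).

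**Step 5: the overall percentage of dippers.** At ρ = 0.5 the reverse flow is (0.40 − 0.2391)/0.60 = 26.8% of dippers. The flows cancel: 0.40 × 40.2% = 0.60 × 26.8% = 16.1% of all patients. Chance reclassification leaves the overall percentage unchanged.

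**Step 6: a controlled contrast.** With three equally correlated recordings (baseline, end of bedtime period, end of daytime period) and no effect, bedtime minus daytime conversion among baseline non-dippers has expectation 0 at any ρ. At ρ = 0.5 about 36% of these patients are discordant, so the 95% half-width is 1.96 × √(0.36/83) = 12.9 percentage points. With all 103 non-dippers (0.40 × 258) it is 11.6.

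**The case against.** **The 0.5 is not the article's figure for this outcome.** A reader might infer that on the plan's own numbers 40% convert by chance. The documents do not support that: 0.5 is stated for the mean arterial pressure calculation, and neither a correlation nor a distribution is given for the ratio. The near-match at 0.5 is one point in a range of 25% to 49%, and at 0.7 or above chance would rarely reach 40%. This objection stands, but even at 0.8 about a quarter of non-dippers convert without an effect.

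**No success criterion is set.** A reader might infer that the trial will be declared positive on conversion if 40% is reached. The article states an expectation and says conversion will be explored; it attaches no test or decision rule to 40%. This stands and lowers the severity. A numerical hypothesis still invites readers to judge it as met or not met.

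**The model may be in an unseen analysis plan.** The absence of a model for an exploratory binary outcome is not a fault in an article, and the design is a randomised, blinded cross-over whose general objective is comparative. That is fair. What remains is the hypothesis as printed, which fixes an absolute threshold without the comparator.

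**The companion hypothesis is different.** The article also expects that "The percentage of individuals who are dippers will increase among the patients undergoing the intervention". A reader might extend the point to it. Step 5 shows why that fails: the whole sample is not selected on dipping, so chance movements in the two directions cancel.

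**Conclusion.** The point holds in limited form. As printed, the hypothesis is an absolute before-after threshold on a dichotomised, variable measure. With no treatment effect, roughly 25% to 49% of baseline non-dippers would convert for ratio correlations from 0.8 down to 0.3. The chance of meeting the threshold ranges from about 0.1% to about 95%, so how easily a null treatment could meet it turns on a correlation the article does not give. Reaching 40% would therefore not be evidence of an effect by itself.

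These figures rest on bivariate normality, the article's 40% prevalence, status assigned at the first baseline, and an assumed correlation. The primary comparison of mean blood pressure is controlled and unaffected, as is the hypothesis on the overall percentage of dippers. Severity: should be fixed, not must be fixed.

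**What to change.** Restate the hypothesis as a controlled one:

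- Among patients with a ratio >0.9 at the first baseline recording, compare within patient the proportion with a ratio ≤0.9 at the end of the bedtime period with that at the end of the daytime period.
- Adjust for period, by a mixed logistic model with treatment, period and a patient random intercept, or by a period-adjusted McNemar-type test.
- Report both proportions and the paired difference with its 95% confidence interval.
- State that 40% against baseline is descriptive only.
- Say whether risers belong to the starting group and whether extreme dippers count as converted.

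The cost is the rewording of one hypothesis and one additional model. It needs no extra patients, visits or recordings: the three recordings used (first baseline and the end of each period) appear in both the text and Table 1. The drawbacks are that the headline becomes a smaller net difference, and that its interval is wide, about ±12 to 13 percentage points under the null at a correlation of 0.5.
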